## 4 STUDY POPULATION

### 4.1 Subject Screening Log

The investigator must keep a record of subjects who were considered for enrolment but were never enrolled, e.g., a subject screening log. This information is necessary to establish that the subject population was selected without bias.

### 4.2 Inclusion Criteria

For inclusion in the study subjects must fulfil all of the following criteria:

1. Provision of informed consent.
2. Male or female aged 18 years or older.
3. Patient with previously confirmed chronic spinal cord injury, **either:**

- a) Traumatic; at any level and any completeness of injury and ASIA grade classification,
  - or
  - b) Non-traumatic; due to infection, inflammation (i.e.; transverse myelitis or ischaemic myelitis), compromised blood supply, a post-ischemic state, etc.
- 4. At least 3 months post spinal cord injury at time of consent.
  - 5. NBD score  $\geq 10$ , confirmed at Baselinea.
  - 6. Only TAI treatment - naïve patient (not having previously used any particular transanal irrigation system, e.g. Peristeen®).
  - 7. Confirmed NBD refractory to conservative therapy and judged eligible for transanal irrigation as per standardised treatment pathway.
  - 8. Able to handle smartphone/tablet.

### 4.3 Exclusion Criteria

Any of the following is regarded as a criterion for exclusion from the study:

- 1. Any confirmed or suspected diagnosis of anal or colorectal stenosis, active inflammatory bowel disease, acute diverticulitis, severe diverticulosis, colorectal cancer, ischemic colitis, history of life-threatening autonomic dysreflexia, bleeding disorders, unspecified peri-anal conditions.
- 2. Untreated rectal impaction.
- 3. Any radiotherapy to the pelvis.
- 4. Any current treatment with anticoagulants (not including aspirin or clopidogrel).
- 5. Any current treatment with long-term systemic steroid medication (not including inhalation agents and/or local topical treatment).
- 6. Current use of prokinetics.
- 7. Any prior rectal or colorectal surgery within 3 months
- 8. Anal, rectal and/or colonic endoscopic polypectomy within the previous 4 weeks.
- 9. Overt or planned pregnancy.
- 10. Ongoing symptomatic UTI as judged by investigator.
- 11. Diagnosed psychiatric illness, considered as unstable by the investigator.

---

a An enrolled subject scoring  $<10$  on the Baseline NBD Score should be discontinued from the study.

12. Diagnosed with MS.
13. Involvement in the planning and conduct of the study (applies to both WHC staff and staff at the study site).
14. Previous enrolment in the present study.
15. Simultaneous participation in another clinical study that may interfere with the present study.

## 4.4 Restrictions

Below restrictions must be applied on all study subjects:

1. No other system for TAI, beside Navina Smart system, may be used during the study period.
2. Each rectal catheter may only be used once.
3. Use of prokinetics is not allowed during study participation.
4. Use of anticoagulants is not allowed during study participation.
5. Use of long-term systemic steroid medication (not including inhalation agents and/or local topical treatment) is not allowed during study participation.
6. Start of opioid (or equivalent) use during the study is prohibited.
7. Stable use (i.e. no change in the last 3 months before enrolment) of laxatives is permitted but should not be altered during the study period.

It is well documented that certain medications can cause or increase faecal incontinence or constipation. Therefore the health care provider/Investigator must review all the medications the patient takes before enrolment into the study and carefully consider if some medications may have the obvious potential to interfere with a successful outcome of the TAI procedure.

## 4.5 Discontinuation of Study Participation

### 4.5.1 Criteria for Discontinuation

Subjects may be discontinued from study participation/treatment at any time. Specific reasons for discontinuing a subject from this study are:

- Voluntary discontinuation by the subject who is at any time free to discontinue his/her participation in the study, without prejudice to further treatment.
- Safety reasons as judged by the investigator and/or WHC.
- Severe non-compliance to protocol as judged by the investigator and/or WHC.
- Incorrect enrolment i.e., the subject does not meet the required inclusion/exclusion criteria for the study.
- Subject lost to follow-up.

Handling of data for discontinued subjects is described in **Section 7.2**.

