## 3 STUDY DESIGN

### 3.1 Overall study design

This Clinical Study Protocol has been subjected to a peer review according to WHC standard procedures.

This study is designed as an open, prospective, non-controlled, qualitative, multicentre study of a novel system for TAI performed in a population of 150 subjects suffering from spinal cord injury, both traumatic and non-traumatic, and confirmed NBD. The main objective is to evaluate the change in NBD symptoms between baseline (before treatment start) and 3 months use of Navina Smart system.

Secondary objectives are to investigate the change of quality of life between baseline (before treatment start) and 3 and 12 months use of Navina Smart respectively, to evaluate improvements regarding constipation, faecal incontinence and frequency of patient reported UTIs, evaluate system compliance, and reasons for non-compliance, perception/satisfaction of the product and therapy as well as short- and long-term efficacy and safety at each follow-up; 3, 6, 9 and 12 months, respectively.

The study is expected to last for a total of 1 year for each subject, with a planned 12 months recruitment period and three scheduled site visits (Baseline, 3 months and 12 months). However, as the yearly incidence of subjects who are considered for TAI treatment is somewhat uncertain, it is recognized that the recruitment period may be prolonged until a sufficient number of evaluable subjects have been reached.

Data will be entered into electronic Case Report Forms (eCRFs) using Viedoc, a web based EDC system. At each irrigation episode, data will be stored in the Navina Smart system unit. The subject will transfer this data to the investigator via a compatible smartphone or tablet using the Navina Smart app.

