## 4.5.2 Procedures for Discontinuation

Subjects not meeting the inclusion/exclusion criteria for this study should, under no circumstances, be enrolled into the study. If subjects not meeting the study criteria are enrolled in error, or where subjects subsequently meet the criteria for discontinuation (see Section 4.5.1) after enrolment, they must be discontinued from study participation/treatment immediately. When applicable, subjects who discontinue prematurely, for any reason, should always be asked about the reason(s) for their discontinuation, the presence of any AE, completion of applicable sections of the eCRF and relevant PROs.

To the furthest extent possible, subjects who discontinue should be seen and assessed by an investigator for follow-up of AE and return of study devices and other study materials.

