### 7.2 Description of Analysis Sets

The study will be analysed using a Per Protocol (PP) and an Intention To Treat (ITT) approach. Subjects fulfilling the inclusion criteria but none of the exclusion criteria and have been treated according to the protocol without any major deviations will be included in the PP analysis set. All correctly included patients will be included in the ITT analysis set. All treated subjects will be included in the safety analysis set. Treatment efficacy related conclusions will be based on the results from the PP analysis and confirmed by an analysis of the ITT analysis set (only for the primary objective) and demography and treatment safety related conclusions will be based on the results from the safety analysis set.

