## 7.5 Statistical Analyses During the Course of the Study

Estimates on minimal important difference and standard deviation may be checked as part of an adaptive statistical design and conditional sample size estimation by interim analysis of a selection of patients, e.g. approximately 60 patients. If the variability is found to be higher and/or the minimal important difference is found to be lower the study is at risk of being inconclusive. In such case additional subjects or premature discontinuation may be considered.

Once the target number of evaluable subjects is secured, i.e. 90% power of the primary variable is verified, partial clean file and analysis of the primary variable and baseline demography will be performed. It is acknowledged that analyses of primary variables and baseline demography will be performed before analyses of secondary variables and analyses of the complete data set. All

analyses will follow the Data Management Plan and be performed on locked data, declared for partial clean file or clean file for the complete data set.

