#### 8.1.1 Navina Smart App Data

The Navina Smart app is running locally on the mobile device and all data associated with the App is stored on a local database. No transferring of data to an external database for central storage is performed, except for anonymous data that is stored for the purpose of data analytics in order to improve the product and the therapy. The App may run without Internet connectivity, even though the creation and sending of reports require internet access.

The Navina Smart app communicates with the Navina Smart unit via Bluetooth Smart protocol, and a checksum is used to validate the correctness of the data transferred. The App has no limits of number of irrigation data to be stored, other than the capacity of the mobile device storage.

The Navina Smart app and its data will stay on the mobile device regardless of the user upgrading the App or the operating system. At deletion of the Navina Smart app, data is deleted, except from anonymous data transferred to Wellspect HealthCare.

Reports sent by email from an App user to site personnel will consist of .pdf and .csv files. The email with the attached reports will automatically contain the Subject ID. The .csv files contain irrigation data and NBD Score data and will be uploaded by site personnel into the subject's eCRF.

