## 8.2 Validation

Data validation will be performed by WHC or its representative.

Data queries will be raised for inconsistent, impossible or missing data. Comments made in Viedoc or ViedocMe in any other language than English will be queried for translation, unless already translated by study site personnel. The study site personnel are required to resolve any such queries. All entries to the study database will be available in an audit trail.

When data has been entered, reviewed, edited and, if applicable, source data has been verified, the data will be locked to prevent further editing and, if not already done, the principal investigator will be prompted to sign the eCRF electronically. Readable copies of the eCRF data, stored on a CD-ROM or a DVD will be archived in the ISF at the study site after Clean File.

The study data will be validated as defined in the Data Management Plan. When all data have been validated, clean file will be declared and the database will be locked.

Study data will be securely stored at WHC, with restricted access.

Data will be retained at WHC 25 years after study closure.

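### Subjects judged severely non-compliant leave study follow-up, and their missing 3-month NBD scores can bias both efficacy sets with no control arm to offset it

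*Protocol*

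**What the plan says.** Section 3.1 of the Protocol describes an "open, prospective, non-controlled, qualitative, multicentre study". The primary outcome is the change in NBD score from baseline to 3 months (2.1).

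- **Discontinuation.** Section 4.5.1 names "Severe non-compliance to protocol as judged by the investigator and/or WHC" as one ground, with no threshold. It introduces the grounds as permissive. Section 4.5.2 says of subjects who meet one of them that "they must be discontinued from study participation/treatment immediately".
- **Discontinued subjects' data.** Section 4.5.1 refers the reader to 7.2. Section 7.2 defines the analysis sets and says nothing on this.
- **Analysis sets.** Under 7.2, PP needs eligibility and treatment without major deviations, and it carries the efficacy conclusions. ITT only confirms the primary objective: "All correctly included patients will be included in the ITT analysis set". Incorrect enrolment may be found after enrolment (4.5.1, 4.5.2).
- **Missing data.** Section 7.1.3 rules out imputation.
- **Who handles the scores.** Section 8.1.1 says of the app files e-mailed to the site: "The .csv files contain irrigation data and NBD Score data and will be uploaded by site personnel".
- **Partial safeguard.** Section 6.4.1 has early withdrawals complete the NBD score at the end of treatment, and 4.5.2 has them asked for relevant patient-reported outcomes.

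**The concern.** The rule links stopping the device to leaving the study. A subject judged non-compliant in the first three months may never give the score that the primary analysis needs, and nothing takes its place. If subjects who do badly are also those who stop complying, the remaining subjects are a favourable selection. A control arm losing subjects in a similar way might absorb part of this, but here there is none, and section 3.3 attributes any change in NBD score to the device.

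The confirming analysis protects less than its name suggests. It does not hold all enrolled or all treated subjects, and it loses anyone without a 3-month pair. The site staff who may judge compliance are also those who receive and upload the NBD files. What is at stake is whether a fall in NBD score reflects the device or the composition of the analysed group.

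**Working it through.** **1. The plan's own figure (7.4).** Inputs: difference 0.8, SD of the paired difference 2.2, two-sided 5%, 90% power.

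N = (1.96 + 1.28)² × 2.2² / 0.8² = 10.4976 × 4.84 / 0.64 = 79.39, so 80. With 150 recruited, 150 − 80 = 70 may be lost, and 70/150 = 46.7%. Both figures reproduce. The allowance treats loss as a matter of precision only, so a large and selective loss would not show up as a shortfall.

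**2. Following a subject through the two sets.**

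| Case | PP | ITT |
|---|---|---|
| Judged non-compliant before month 3, no 3-month score | Out, if severe non-compliance counts as a major deviation | Member, but no pair, so contributes nothing |
| Same, with an end-of-treatment score | Out | Member; the Protocol does not say whether this score counts in the 3-month comparison |
| Judged non-compliant after month 3 | Out, if the deviation is called major; the score already exists | Member, pair retained |
| Found ineligible after enrolment | Out | Out, whatever the score |

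**3. How far selection moves the result.** Assumptions: no true change, change distributed N(0, 2.2), and a fraction *f* of the worsened subjects removed at random. SD, test and level are the Protocol's. The removal pattern and 90 evaluable subjects are assumed; the Protocol's own numbers are 80 and 150.

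Half the subjects worsen, by 2.2 × √(2/π) = 1.755 on average. The mean of those left is −(0.5 × *f* × 1.755) / (1 − 0.5 × *f*). False-positive rates come from 20,000 simulated trials per setting (two-sided 5% Wilcoxon signed-rank test).

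| *f* | Share of all subjects removed | Mean change | False-positive rate |
|---|---|---|---|
| 0 | 0% | 0 | 4.6% |
| 10% | 5% | −0.088/0.95 = −0.09 | 7.2% |
| 20% | 10% | −0.176/0.90 = −0.20 | 14.1% |
| 30% | 15% | −0.263/0.85 = −0.31 | 26.9% |

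**4. Other patterns.** If the 2, 5 or 10 worst of 90 are removed, the mean change is −0.12, −0.26 or −0.46 and the false-positive rate 7.4%, 16.3% or 44.5%. This is perfect selection on outcome and marks the upper end. In a separate run with 150 enrolled, removal was only correlated with the change (0.3 to 0.5). Losing 10% then gave −0.12 to −0.22 and 9% to 20%; losing 20% gave −0.23 to −0.38 and 20% to 48%.

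**The case against.** A reader might infer that the investigator and sponsor can prune both efficacy sets with the primary outcome in view. The documents do not support that, for these reasons.

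- **ITT is narrowed by eligibility, not compliance.** Withdrawal for non-compliance leaves a subject in ITT by definition. Eligibility is verified before a subject ID is allocated (3.2, 4.6). The loss from ITT is only in effect, through a missing score.
- **Timing.** A withdrawal before month 3 cannot be made with the 3-month value in view, though app self-evaluations may be seen earlier (5.1.2.1, 5.3). A withdrawal after month 3 leaves the pair collected. Exclusion with the score visible is thus mainly a PP matter.
- **Sponsor visibility is inferred.** Section 8.2 says "Data validation will be performed by WHC or its representative", and 7.5 allows an "interim analysis of a selection of patients, e.g. approximately 60 patients". Neither says that those who judge compliance see the scores. For site staff it is explicit.
- **Unseen documents.** What counts as a major deviation, who decides and when may stand in the SAP. Section 7.2 names no decider, and 7.5 requires locked data. Silence on these points is no finding.
- **The simulated patterns are assumed.** They are one-sided or outcome-linked by construction, and the Protocol offers no evidence that poor responders comply poorly.

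All of this stands and narrows the point. What remains is fixed in the Protocol: participation ends on a judgement of non-compliance, missing scores are not imputed, PP carries the conclusion, ITT is restricted, and the reference to 7.2 leads nowhere. An SAP cannot supply a 3-month score that was never collected.

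**Conclusion.** The concern holds as an opening for favourable bias; nothing shows that bias occurred. It is strongest for PP, which carries the efficacy conclusion, and weaker for ITT, where it acts through missing 3-month pairs and through inclusion status revised after enrolment. Its direction depends on non-compliance going with poor response, which is plausible but not documented.

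The size is unknown. With 10% to 30% of worsened subjects removed, the shift is about 0.09 to 0.31 points, or 12% to 39% of the 0.8-point target (0.0924/0.8 and 0.310/0.8), and the false-positive rate is roughly 7% to 27%. Higher rates need stronger or more extensive selection. Separately, and without any assumption, 4.5.1 and 7.2 do not fit together on discontinued subjects' data and must be reconciled. The change is worth making because it is cheap and protects the only check on the PP result.

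**What to change.** Leave decisions on stopping treatment as they are, and separate them from study follow-up:

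1. State that a subject judged non-compliant is still asked for the scheduled 3-month NBD score and is kept in ITT. This does not bind subjects who withdraw voluntarily.
2. Limit incorrect inclusion, as a reason to leave ITT, to eligibility facts recorded before the first irrigation.
3. Have major deviations and eligibility exclusions settled by persons without access to post-baseline NBD scores, before those scores are released for analysis. If the SAP already does this, a cross-reference is enough.
4. Write into 7.2 the rule for discontinued subjects' data that 4.5.1 promises, including whether an end-of-treatment score enters the 3-month comparison. Reconcile the permissive wording of 4.5.1 with the mandatory wording of 4.5.2.

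The cost is protocol wording, an access setting in the data capture system and some extra follow-up contacts. The downside is that the ITT estimate includes poor compliers and may be slightly less favourable. The fix leaves PP as the basis for efficacy, so that estimate still omits major deviators, but ITT becomes a more useful check on it.

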## 4.5.2 Procedures for Discontinuation

Subjects not meeting the inclusion/exclusion criteria for this study should, under no circumstances, be enrolled into the study. If subjects not meeting the study criteria are enrolled in error, or where subjects subsequently meet the criteria for discontinuation (see Section 4.5.1) after enrolment, they must be discontinued from study participation/treatment immediately. When applicable, subjects who discontinue prematurely, for any reason, should always be asked about the reason(s) for their discontinuation, the presence of any AE, completion of applicable sections of the eCRF and relevant PROs.

To the furthest extent possible, subjects who discontinue should be seen and assessed by an investigator for follow-up of AE and return of study devices and other study materials.

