**Weekly Telephone follow-up**

- Investigator or delegate will make a telephone call to the subject once per week until a feasible and satisfactory routine has been established, as agreed by both subject and investigator or delegate. The follow-up phone calls will be initiated by the therapist with the intention of identifying optimal performance and outcomes of irrigation, based on irrigation reports sent to site by the subject. If there are specific problems reported by the patient, or there is inadequate efficacy of treatment the therapist will advise tailoring of the TAI regime according to the Navina Treatment Schedule (see Appendix C). The health

status and compliance to the therapy will be monitored and collection of any AE and SAE will be performed.

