**Table 6 Outcome Variables**

| Objective                                                                                                     | Outcome Variable | Method                                                                                                                                                                                                                                                          |
|---------------------------------------------------------------------------------------------------------------|------------------|-----------------------------------------------------------------------------------------------------------------------------------------------------------------------------------------------------------------------------------------------------------------|
| To investigate change in NBD symptoms between baseline and 3 months use of Navina System (primary objective). | NBD score.       | Analyses of absolute values and change between measurements according to instructions from the provider of the validated Neurogenic Bowel Dysfunction Score  (NBD Score) at Baseline (Visit 1) and 3 months (Visit 2).
See section 6.4.1 |

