## 6.4 Patient-Reported Outcomes (PROs)

### 6.4.1 The Neurogenic Bowel Dysfunction score

To evaluate the effect of Navina System, a patient friendly version of the validated standardized NBD score  questionnaire will be used. The NBD score is a symptom-based score for neurogenic bowel dysfunction that takes into account both constipation and faecal incontinence, and weighs each symptom of NBD according to its impact on QoL in persons with spinal cord injury. The NBD score has a 10-item symptom severity scale to measure the parameters, faecal incontinence, constipation and obstructed defecation.

Each item is assigned a score based on odds ratios for associations between items and impact on QoL. Negative changes in NBD score correspond to an improvement in bowel-related symptoms, and the total NBD score can range from 0 (very minor bowel dysfunction) to 47 (severe bowel dysfunction).

The NBD score is self-administrated and will be completed by all subjects at baseline (visit 1), at 3 months follow-up (visit 2), in connection to the 6 and 9 months telephone follow-ups and at 12 months follow-up (Visit 3) or at end of the treatment period for those subjects with early withdrawal from the study. The subject will be provided with personal log-in details to *Viedoc™Me*, the patient interface of the eCRF, which will be used to complete the NBD score at baseline. The NBD score at 3, 6, 9 and 12 months follow-up will be completed using the Navina Smart app (see further instructions in 5.1.2). If, at any time during the study and for any reason,

the subject is unable to complete web-based questionnaires, the subject will be provided a paper questionnaire. Study site personnel will then enter the data into the study data base.

Applicable scores and results from the questionnaire will be analysed and presented according to the user instructions from the provider. The results from the NBD score at baseline and at the 3, 6, 9 and 12 months follow-up will be compared.

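### Formal discontinuation before month 3 leaves correctly included subjects in the ITT set with at most an exit NBD score and no month-3 score

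*Protocol*

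**What the plan says.** Section 4.5.1 lists the reasons for discontinuation: the subject's own choice to leave, safety, "Severe non-compliance to protocol as judged by the investigator and/or WHC", incorrect enrolment, and loss to follow-up. It adds: "Handling of data for discontinued subjects is described in" Section 7.2. Section 4.5.2 requires that subjects who meet a criterion after enrolment be removed at once: "they must be discontinued from study participation/treatment immediately". They are asked for the reason, adverse events and relevant questionnaires, and should return the device. Section 4.6 bars re-entry.

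Section 6.4.1 schedules the NBD score at baseline and at 3, 6, 9 and 12 months, "or at end of the treatment period for those subjects with early withdrawal from the study". Table 6 defines the primary outcome by the scores at baseline and Visit 2, and Table 3 gives Visit 2 a window of 2 weeks either side of 3 months.

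Section 7.2 bases efficacy conclusions on the PP set and confirms them in the ITT set, for the primary objective only. On membership it says: "All correctly included patients will be included in the ITT analysis set". Section 7.1.3 excludes imputation.

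**The concern.** A confirmatory ITT analysis is useful because it includes subjects whom the PP set leaves out, here those taken off the device for harm or poor adherence. Under 4.5 such a subject leaves data collection together with the device. If that happens before the month-3 window, the subject counts as ITT but contributes no primary change.

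The ITT analysis then rests mainly on subjects still in the study at month 3. That is close to the group PP already describes, so agreement between the two is weaker support than it appears. The scores not collected are also likely to come from subjects who did less well. The collection rule has to be set before the scores fall due. A statistical analysis plan (SAP) can give the exit score a role, but it cannot create a month-3 score.

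**Working it through.** **1. The plan's own figure.** Section 7.4 uses a difference of 0.8, an SD of 2.2, 90% power and 5% two-sided significance:

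N = (1.96 + 1.28)² × 2.2² / 0.8² = 10.4976 × 4.84 / 0.64 = 79.4, rounded up to 80.

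150 − 80 = 70, and 70/150 = 47%. The stated figures reproduce. This checks the arithmetic only, not the inputs. The 80 are subjects with 3 months of device use, so the point made here does not change that number.

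**2. Timing.** Three months is about 13 weeks, so the Visit 2 window is weeks 11 to 15. During the early weekly calls the subject's health "status and compliance to the therapy will be monitored and collection of any AE and SAE will be performed". A safety or non-compliance exit can therefore come well before week 11.

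**3. One subject followed through the text.** Take a correctly included subject discontinued for safety in week 3.

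- 4.5.2: participation and treatment end in week 3.
- 6.4.1: an NBD score is due in week 3, and no later one is planned.
- 4.6: the subject cannot return.
- 6.4.1 and 5.1.2.1: the month-3 score is normally entered in the app, which needs access to the control unit, and the device goes back at exit. A paper route exists, but nothing calls for it after exit.
- 7.2: the subject is in the ITT set.
- Table 6: the primary change needs a Visit 2 score, and there is none.
- 7.1.3: no value is imputed.

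An exit score in week 10 would be close to the window. One in week 3 is not.

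**4. Who is affected.** Incorrect enrolments are outside the ITT set, and subjects lost to follow-up cannot be recovered by wording. Stopping irrigation is not itself a criterion in 4.5.1, and the compliance item in Tables 1 and 6 asks at 3 and 12 months whether the subject still irrigates. A subject who stops without being formally discontinued keeps the scheduled scores. What remains is mainly safety and severe non-compliance exits before about week 11, plus any voluntary leavers still willing to answer.

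**5. Size, under assumptions.** Let e be the number of subjects whose month-3 score is recovered, S the number of other scored subjects, and g the gain in the recovered subjects. The others are assumed to gain 4.5 points, the mean that 7.4 cites from an earlier irrigation study.

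Fall in ITT mean gain = e / (S + e) × (4.5 − g)

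The protocol gives no e. The assumed values are 5, 10 and 20, with S from 80 (the plan's minimum) to 150 − e, and g either 0 (back at baseline) or 2.25 (half the gain kept).

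| e | g = 0, S = 80 | g = 0, S = 150 − e | g = 2.25, S = 80 | g = 2.25, S = 150 − e |
|---|---|---|---|---|
| 5 | 0.26 | 0.15 | 0.13 | 0.08 |
| 10 | 0.50 | 0.30 | 0.25 | 0.15 |
| 20 | 0.90 | 0.60 | 0.45 | 0.30 |

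For the largest entry, 20/100 × 4.5 = 0.90, which leaves a mean gain of 4.5 − 0.9 = 3.6. The planned test is the Wilcoxon signed rank test, so these means illustrate scale and are not the test result.

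**The case against.** **The wording is not explicit.** The slash between participation and treatment could mean either or both. That is true, but the title of 4.5 (study participation), the re-entry bar in 4.6 and the exit-score rule in 6.4.1 all favour joint termination.

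**The group is small.** The voluntary criterion in 4.5.1 is a choice to leave the study, not just the device, and severely non-compliant subjects may not complete questionnaires. This stands and narrows the point mainly to safety and non-compliance exits.

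**No conclusion changes.** Even the worst tabulated case leaves a gain of 3.6, which is 4.5 times the 0.8 the plan wants to detect. This also stands. The 0.8 is a gain from baseline worth detecting, not a tolerance for disagreement between PP and ITT, so it should not be used to call the fall large.

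**The target is change under use.** The primary objective and the sample size refer to 3 months of use, and PP carries the conclusions. That is fair for PP, but the protocol itself chose ITT as confirmation for the primary objective. A confirmation that lacks scores from subjects taken off the device confirms less.

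**The remedy can contaminate the result.** Section 3.3 attributes any NBD change to the study device, and a score obtained on a competing irrigation system would undercut that. This stands, so such scores need to be identified and separated.

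**Part of this belongs in the SAP.** A reader might infer that the protocol is at fault because 7.2, to which 4.5.1 refers, does not say which score counts for discontinued subjects. That choice is commonly left to the SAP, which is not shown, and it is no part of the finding. What remains is the collection rule.

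**Conclusion.** The point holds in a limited form. Followed as written, 4.5 and 6.4.1 leave correctly included subjects who are discontinued before the month-3 window without a month-3 score, and the confirmatory ITT analysis leans towards those who stayed. The number affected is unknown. With 5 to 20 recovered subjects the ITT mean gain falls by 0.08 to 0.90, if the others gain 4.5 points and recovered subjects keep half or none of that. A handful of such exits changes little. The PP analysis and the sample size are unaffected.

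Two stronger readings go beyond the documents. A reader might infer that up to 70 of 150 subjects will lack a month-3 score. The 70 is a tolerance, and 7.4 does not split it by timing or reason. Power of about 0.65 for an ITT analysis of all 150 results only if all 70 leave before month 3, all have zero change, and the true gain in the other 80 is just 0.8 (mean 0.8 × 80/150 = 0.43). A reader might also infer that anyone who stops irrigating loses the primary score, but the compliance item shows that non-users are expected at visits.

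This is a cheap improvement to a secondary check, not a flaw in the main result.

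**What to change.** In 4.5, separate stopping the device from leaving the study. State that subjects who stop the device and do not withdraw consent still complete the month-3 NBD score, within the 2-week window either side, on paper or by phone. Keep the exit score, label it as end of device use, and do not treat it as a month-3 value.

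After the stop, do not hold these subjects to the 4.4 limits on other irrigation systems and laxative changes, but record any new bowel treatment. Use the month-3 scores in the ITT analysis of the primary objective, with a sensitivity analysis that excludes scores obtained after starting another irrigation system or changing laxatives. Leave PP as planned. Later NBD scores, the EQ-5D-3L and the Follow-up Questionnaire after stopping are optional.

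The cost is an amendment to the wording and a few extra questionnaires, using the paper route already in 6.4.1. Some subjects will decline, some scores will reflect other bowel treatment, and the ITT effect may be smaller.
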